### Interim analyses {21b}

Although there are no anticipated problems that may be detrimental to the participants, serious life-threatening AEs leading to prolonged hospital stay or death will be reported to the IRB and our study will be terminated immediately.

### Methods for additional analyses (e.g., subgroup analyses) {20b}

For the primary outcome, multivariate analysis will be used to determine possible confounding factors, such as age, sex, BMI, intraoperative opioid dose, operation time, anesthesia time, surgical site, tumor types, and tumor size. Subgroup analysis will be conducted to evaluate outcomes in patients based on the site of surgery (age, sex, duration of surgery, preoperative pain severity).

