#### Exclusion criteria

History of chronic headache or chronic pain syndrome of any cause, psychiatric disorders or uncontrolled epilepsy;Inability to understand or use the pain scales before surgery;Excessive alcohol or drug abuse, chronic opioid use (more than 2 weeks or 3 days per week for more than 1 month), use of drugs with confirmed or suspected sedative or analgesic effects, or use of any painkiller within 24 h before surgery;Request of oral/intravenous glucocorticoid to decrease cerebral edema within 1 week before surgery;Pregnancy or breastfeeding;Extreme body mass index (BMI) (< 15 or > 35);Participation in another interventional trial that interferes with the intervention or outcome of this trial;Refusal or inability of the patient and/or legal guardian to provide informed consent;Coagulopathy;Infection around the puncture site; andHistory of allergies to any of the study drugs.

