#### Anesthesia protocol

All participants will be informed about the REDUCE trial during a pretreatment visit. Each participant will be equally randomized to one of the groups using a closed envelope technique. After the patient arrives in the operating room, standard monitoring, such as a 5-lead electrocardiogram, heart rate (HR), pulse oximetry, and noninvasive arterial blood pressure (BP) will be recorded. Induction will be carried out with 2 to 3 mg/kg propofol and 0.3 to 0.5 μg/kg sufentanil. Neuromuscular blockade will be performed with 0.6 mg/kg I.V. rocuronium to facilitate tracheal intubation.

After induction, anesthesia will be maintained with 4 to 8 mg/kg/h propofol and 0.1 to 0.3 μg/kg/min remifentanil at the discretion of the attending anesthesiologist. Remifentanil will be adjusted according to the degree of surgical stimulation. Additional boluses of remifentanil (0.5 μg/kg/bolus) will be administered to decrease any significant response to surgical stimulation. Meanwhile, the infusion rate of remifentanil will be increased by 0.05 μg/kg/min. No additional sufentanil will be used intraoperatively. We will use mechanical ventilation through an endotracheal tube with a mixture of oxygen in air (fraction of inspired oxygen (FiO2) 0.5 to 0.6) with end-tidal carbon dioxide between 35 and 45 mmHg. The intraoperative HR and BP will be maintained within 20% of the baseline levels. An increase or decrease in the mean arterial pressure (MAP) from the baseline value by more than 20% will be considered clinically significant and will be treated with nicardipine or dopamine. Nicardipine or dopamine will be administered with intermittent boluses and with continuous infusion if necessary. The number of patients who receive nicardipine or dopamine will be recorded. The intraoperative HR and BP will be recorded before anesthetic induction, after anesthetic induction, 5 min after intubation, and at the insertion of cranial pins, skin incision, skull drilling, dura mater opening, and skin closure. Similarly, any significant elevation or reduction in HR and BP will be noted throughout the operation. The dosages of all drugs and intraoperative physical parameters will be closely monitored and recorded by the investigator.

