#### Scalp nerve blocks

The anesthesiologist will perform scalp nerve blocks based on the group allocation 10 mins before the incision. Scalp nerve blocks will be performed according to the technique previously described by Pinosky et al. [14]. The following nerves will be blocked bilaterally: the supraorbital and supratrochlear nerves will be blocked with 2 ml of solution injected, at the point where they emerge above the orbit, above the midline of the eyebrow perpendicular to the skin and superficial to the periosteum; the zygomaticotemporal nerves will be blocked using 2 ml of solution midway between the supraorbital and auriculotemporal nerves; the auriculotemporal nerves will be blocked with 3 ml of solution of 1.5 cm in front of the ear at the level of the tragus. The needle will be perpendicular to the skin and 1.5 ml will be injected in the deep fascia, while another 1.5 ml will be superficially injected during the needle extraction; the postauricular branches of the greater auricular nerves will be blocked with 2 ml of solution 1.5 cm posterior to the tragus of the ear, between the skin and bone; the greater, lesser, and third occipital nerves will be blocked with 2 ml of solution injected along the superior nuchal line, approximately midway between the occipital protuberance and the mastoid process. The total volume of the solution used for scalp nerve blocks will be 22 ml in all participants.

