## Data collection and management

### Plans for assessment and collection of outcomes {18a}

After obtaining written informed consent, baseline data, including age, sex, BMI, intraoperative opioid dose, operation time, anesthesia time, surgical site, tumor types, and tumor size, will be collected by an independent researcher. The PCA press will be recorded by an electronic memory system in real time. The information of PCA press including the first press of PCA demand button and the cumulative amount of sufentanil consumption can be directly extracted. In order to ensure postoperative analgesia quality, an acute pain management team will monitor the pain pump remotely and deal with problems, such as congestion and battery drain, on time. An independent clinical resident who is not involved with the group allocation will complete a follow-up at 2, 4, 8, 12, 16, 20, 24, and 48 h after surgery.

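### The multivariate analysis of analgesia duration treats intraoperative opioid dose, operation time and anesthesia time as baseline confounders, although they are wholly or largely determined after the block

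*Protocol article*

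**What the plan says.** Under Methods for additional analyses {20b}, the article states for the primary outcome that "multivariate analysis will be used to determine possible confounding factors", and gives as examples "such as age, sex, BMI, intraoperative opioid dose, operation time, anesthesia time, surgical site, tumor types, and tumor size". The same section names subgroup factors in brackets after site of surgery: "age, sex, duration of surgery, preoperative pain severity".

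Under Plans for assessment and collection of outcomes {18a}, the same variables are collected as "baseline data, including age, sex, BMI, intraoperative opioid dose, operation time, anesthesia time, surgical site, tumor types, and tumor size". Table 1 marks its baseline row in the surgery column as well as before surgery.

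The timing is set elsewhere. The solution is injected after induction (Intervention and control groups), "based on the group allocation 10 mins before the incision" (Scalp nerve blocks). Under Anesthesia protocol, "Remifentanil will be adjusted according to the degree of surgical stimulation", and no sufentanil is given after the induction dose. The primary outcome runs from the block to the first postoperative press of the PCA button (Primary outcome), and the pump is provided on arrival in the PACU or ICU (section {11d}).

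Pain scores are scheduled only from 2 h to 48 h after surgery (Secondary outcomes and Table 1). The only preoperative mention of pain scales is an exclusion criterion: "Inability to understand or use the pain scales before surgery".

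**The concern.** Randomisation protects the comparison only for what is fixed before allocation. A variable that arises after treatment cannot confound a randomised contrast, but it can carry part of the treatment effect, or share an unmeasured cause with the outcome. Conditioning on such a variable changes what the treatment coefficient estimates.

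Opioid dose is the clearest case. After induction it varies only through remifentanil, which follows the response to stimulation, and a scalp block acts on that response. The Background postulates that dexamethasone improves block quality and reduces opioid consumption, without saying that this includes intraoperative remifentanil.

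What is at stake is how the adjusted result will be read. The Discussion relies on the multivariate analysis to deal with BMI as a confounder, so readers are likely to take its treatment coefficient as the better-controlled estimate. With opioid dose in the model, that coefficient may not answer the randomised question. Separately, a subgroup factor that no section schedules may turn out to be unavailable or inconsistently recorded.

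**Working it through.** **1. When each variable is settled.**

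- Age, sex, BMI, surgical site, tumor type and tumor size belong to the patient or lesion and do not depend on the block.
- Operation time falls wholly after the block, which is given 10 min before incision.
- Anesthesia time starts before the block, but most of its variation comes from the length of surgery.
- Intraoperative opioid dose has a pre-block part (induction sufentanil and any remifentanil before the injection) and a larger titrated part after it.

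**2. Operation time and the outcome.** Block to first press = 10 min + operation time + time from end of surgery to the pump + time from pump to first press. Operation time is therefore a component of the outcome, not a baseline cause of it.

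**3. What adjusting for opioid dose can do.** The documents give no figure for this, so what follows is illustration. The 180 min (30% of 600) and the SD of 240 min come from the Sample size section; every other input is assumed.

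*Shared cause only.* Let M be opioid dose in SD units, g the arm, and U unmeasured pain sensitivity that explains half the variance of M:

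- M = −s·g + √0.5·U + √0.5·e
- Y = 600 + 180·g − c·U + noise, total within-arm SD 240

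The within-arm slope of Y on M is −√0.5·c, so the adjusted effect is 180 − 0.707·c·s. Taking c = 60 or 120 min per SD means that U explains 60²/240² = 6.25% or 120²/240² = 25% of the outcome variance.

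| Fall in dose, s | c | Bias (min) | Adjusted effect (min) |
|---|---|---|---|
| 0 | either | 0 | 180 |
| 0.3 | 60 | 12.7 | 167.3 |
| 0.5 | 60 | 21.2 | 158.8 |
| 0.3 | 120 | 25.5 | 154.5 |
| 0.5 | 120 | 42.4 | 137.6 |

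A simulation of 2,000 runs with 70 per arm gave 167, 158, 152 and 137 for the last four rows, a bias of 13 to 43 min. The unadjusted estimate stayed at about 179. This model has no path from dose to outcome, so the bias comes entirely from conditioning on a variable that shares a cause with the outcome.

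*Adding a direct path.* Suppose instead that each SD of opioid dose shortens analgesia by 0.3 × 240 = 72 min, with the total effect held at 180.

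- No shared cause: the adjusted effect is 180 − 72·s, which is 162 at s = 0.25 and 144 at s = 0.5 (simulated 162.6 and 144.2).
- With a shared factor correlated 0.5 with dose and worth another −72 min per SD, the slope is −72 − 0.5 × 72 = −108. The adjusted effect is then 180 − 108·s, or 153 and 126 (simulated 153.1 and 125.6).
- At s = 0 the adjusted effect stays at about 180 in both.

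**4. Preoperative pain.** The subgroup list names it. The {18a} list does not, and the NRS row of Table 1 begins at 2 h after surgery. The exclusion criterion concerns the ability to use a scale, not a recorded score.

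**The case against.** The strongest reply is that this is only an additional analysis. The group comparison under Statistical methods {20a} is an unadjusted t test or Wilcoxon-Mann-Whitney test. That is right, and a reader who inferred that the primary result is biased would be going beyond the text. The wording can also be read as a search for prognostic factors rather than a fixed adjusted estimate. That reading is possible, but the section calls the variables confounders, and a multivariate model that includes arm will yield an adjusted treatment effect.

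Second, nothing shows that dexamethasone changes intraoperative opioid dose. Both arms receive the same volume and strength of bupivacaine with epinephrine; only the 1 ml additive differs, and the main hypothesis concerns duration. This also stands. A reader might infer that opioid dose is an established mediator, but the documents support only that it may be one. For that reason the range of bias must begin at 0.

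Third, the three variables are not alike. Surgeons are blinded, and nothing suggests that 4 mg of dexamethasone in a scalp block alters surgical time. If it does not, adjusting for operation time causes no such bias and may mainly remove noise. Opioid dose and anesthesia time are also partly pre-block. These points limit the concern, but they do not make the variables baseline.

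Fourth, the {18a} list is introduced as non-exhaustive, and an article need not reproduce every CRF field. One might infer that the preoperative-pain subgroup cannot be done; the text supports only that its measurement is not scheduled in the article.

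**Conclusion.** The concern holds for the adjusted model and for the labelling. The article presents three variables that are wholly or largely post-block as baseline data and as possible confounders of a randomised comparison. Opioid dose carries the real risk, because it is titrated to a response that the block may alter. Operation time is part of the outcome interval and so not a confounder, but bias from it is unlikely unless treatment affects surgical time. The same applies to the duration-of-surgery subgroup.

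The size is unknown. It is 0 if dexamethasone leaves opioid dose unchanged. It is roughly 13 to 43 min of a 180-min effect if the dose falls by 0.3 to 0.5 SD and pain sensitivity drives half the dose variance and about 6% to 25% of the outcome variance. For scale, the protocol's minimally important difference is 60 min. These inputs are assumptions, and the other illustrative model, with a direct path, gives biases of the same order (18 to 54 min for a fall of 0.25 to 0.5 SD). The unadjusted primary comparison is untouched, so this is worth correcting but does not threaten the main result.

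Preoperative pain severity is a smaller inconsistency: a named subgroup factor without a scheduled measurement.

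**What to change.** - Limit the adjusted treatment-effect model to pre-randomisation factors: age, sex, BMI, surgical site, tumor type and tumor size.
- Report intraoperative opioid dose, operation time and anesthesia time by arm as intraoperative results, and remove them from the baseline list in {18a}.
- Label any model or subgroup that uses them, including duration of surgery, as exploratory and not confounder-adjusted.
- For preoperative pain severity, state where it is recorded. If it is not already on the CRF, add a preoperative NRS to Table 1 and the CRF, or drop the subgroup.

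The cost is wording in the protocol and the SAP, which the article says will be fixed before database lock, and at most one CRF field. Recruitment began in December 2020, so if the score is not yet collected, patients enrolled before the change will lack it.

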### Methods in analysis to handle protocol non-adherence and any statistical methods to handle missing data {20c}

We will perform a modified intention-to-treat (ITT) analysis and participants who are randomized after enrollment and receive at least one of the study interventions will be analyzed. For per-protocol (PP) analysis, participants who withdraw from the study will be excluded from the analysis. Sensitivity analysis will be performed as an additional evaluation with the PP set, and the results will be compared with those of the modified ITT analysis. Missing observations will be replaced with the last observation carried forward.

### Plans to give access to the full protocol, participant level-data and statistical code {31c}

Study protocol, statistical analysis plan, analytic code will be available beginning 9 months and ending 36 months after article publication. Investigators whose proposed use of the data has been approved by an independent review committee identified for this purpose. Proposals should be directed to [contact]. Meanwhile, to gain access, data requestors will need to sign a data access agreement.

### Composition of the data monitoring committee, its role and reporting structure {21a}

The Data Monitoring Committee (DMC) will comprise of a statistician, a neurosurgeon, an anesthesiologist, and a pain physician. They will conduct an independent review of data collection and patient safety. The DMC will report directly to TSC at their meeting after every 25%, 50%, 75%, and 100% of patient inclusions.

### Adverse event reporting and harms {22}

An AE will be defined as any untoward medical occurrence such as local hematoma, nerve injury, intra-arterial injection, allergic or toxic reaction, or facial nerve paralysis from scalp nerve blocks. Patients with blurry vision and tinnitus will be carefully observed postoperatively. Meanwhile, any signs of glucocorticoid-associated systemic toxicity such as infection will also be addressed according to the current practices and will be recorded. SAEs will include death, immediate life-threatening conditions, coma, inpatient hospitalization, or prolongation of the existing hospitalization. Serious adverse events (SAEs) occurring in the REDUCE trial must be signed and submitted to the trial management committee within 24 h after they are recognized. All SAEs that occur (including SAEs in withdrawn participants) must be continuously monitored until there are no signs or symptoms or until the participants are in stable condition. Anonymized data on all AEs must be annually reported to the IRB.

### Frequency and plans for auditing trial conduct {23}

The IRB will monitor the research process of the REDUCE trial regularly and the progress report will be submitted to IRB annually.

### Plans for communicating important protocol amendments to relevant parties (e.g., trial participants, ethical committees) {25}

Any amendments will be submitted to the IRB, and the IRB will also be informed of the end of the REDUCE trial. All changes will be recorded. Any change will be applied to all subsequent patients, and the registration record will be updated.

### Dissemination plans {31a}

At the completion of the trial and following publication of the primary and secondary outcomes, requests for data sharing will be considered by the REDUCE trial Management Group. The results of the trial will be published in peer-reviewed journals. Both positive and negative results will be reported.

## Discussion

This randomized controlled trial will evaluate the effects of dexamethasone as an additive to bupivacaine in scalp nerve blocks for postcraniotomy pain relief. The REDUCE trial will employ scalp nerve blocks by blocking several different nerves on both sides and describe a postcraniotomy analgesia method for scalp nerve blocks with improved quality and prolonged duration.

Regarding the “off-label” use of perineural adjuvants, the safety of dexamethasone is rather promising. So far, no clinical trial has reported neurotoxicity due to perineural dexamethasone. In the in vivo models, dexamethasone could produce reversible nerve block without long-term motor or sensory deficits or sciatic/dorsal root ganglion damage after a single injection or even continuous injection for 15 days [44]. More reassuringly, epidural injection of glucocorticoid is a common method for the treatment of cervical and lumbar nerve root pain and the safety of adding dexamethasone to epidural bupivacaine has already been proved [45]. The neurological risk of local dexamethasone, if any, seems small. This study will also undoubtedly pay close attention to the AEs of perineural dexamethasone.

The current protocol also has some limitations. First, we will use a single dose of dexamethasone and will not clarify the dose-effect relationship between the dose of dexamethasone and the effectiveness of pain relief. Second, we do not measure the blood concentration of dexamethasone. Systemic administration of dexamethasone has often been used for reducing cerebral edema and as a prophylaxis for PONV in clinical practice. A single dose of dexamethasone is also unlikely to cause systemic toxicity. According to previous literature, only 4 mg of dexamethasone will be administered. Third, all drugs that are part of the scalp block will not be administered on the basis of the patient’s weight. Although BMI will be considered in the multivariate analysis, it is still an inevitable potential confounding factor. Varin et al. reported that the distribution of ropivacaine after a femoral nerve block was significantly affected by body weight, but none of the pharmacodynamic model parameters showed weight dependence [46]. Whether the distribution of local anesthetics after scalp nerve blocks is significantly affected by body weight is yet to be investigated. Finally, this is a single-center trial, and it will be necessary to carry out a multicenter clinical study to provide higher levels of evidence.

If the results are positive, we may validate the use of dexamethasone as an effective adjuvant to local anesthetics for alleviating postoperative craniotomy pain and prolonging the duration of nerve blocks without associated side effects. The results of the REDUCE trial may influence future guidelines on postoperative analgesic techniques for craniotomy.

## Trial status

The research protocol (protocol version 3.2/2018-07-05) is approved by the IRB of Beijing Tiantan Hospital, Capital Medical University. Recruitment of patients for the REDUCE trial started in December 2020, and the trial is expected to be complete in 2022.

## Abbreviations

NSAIDs: Nonsteroidal anti-inflammatory drugs
SPIRIT: Standard Protocol Items: Recommendations for Interventional Trials
ASA: American Society of Anesthesiologists physical status
GCS: Glasgow Coma Scale
AEs: Adverse events
HR: Heart rate
BP: Blood pressure
MAP: Mean blood pressure
IRB: Institutional Review Board
PACU: Postanesthesia care unit
ICU: Intensive care unit
PCA: Patient-controlled analgesia
NRS: Numeric Rating Scale
CRF: Case report form
PONV: Postoperative nausea and vomiting
SAS: Sedation Agitation Scale
LOS: Length of stay
PSS: Patient satisfaction score
SD: Standard deviation
ANOVA: Analysis of variance
DMC: Data Monitoring Committee
SAEs: Serious adverse events
CONSORT: Consolidated Standards of Reporting Trials
